### Secondary objective/endpoints

Secondary end-points include; the individuals components of the primary composite end-point, incidence of metabolic syndrome as defined by the International Diabetes Federation (IDF) [11,12], incidence of pre-hypertension as defined by Joint National Committee on Prevention, Detection, Evaluation, and the Treatment of High Blood Pressure (JNC-7) [13], regression of IGT and IFG, [IGT and IFG will be defined as per World Health Organisation (WHO) and American Diabetes Association criteria [14,15]] and changes in: weight, BMI, waist circumference (WC), fasting triglycerides, fasting high density lipoprotein (HDL) and low density lipoprotein (LDL) cholesterol, serum creatinine and estimated glomerular filtration rate (GFR), physical activity as measured by the International physical activity questionnaire (IPAQ)[16], depression, as measured by PHQ-9 questionnaire, [17], and psychological stress, as measured by perceived stress scale [18]. Adherence to diet and physical activity will be self-reported based on weekly pattern and evaluated at study visits. The effects of baseline risk factors on the development of end-points will also be evaluated in analyses.

Quality of life measures will be evaluated using a validated short version of the multidimensional WHO Quality of Life questionnaire (WHOQOL-Bref) [19]. Health economic analyses by the Public Health Department University of Colombo with advice and guidance from Division of Social Care and Policy at King's College London is an area we plan to develop utilising models described in recent studies [20].

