#### Procedures

The following procedures and measurements will be performed at baseline prior to randomisation to one of the two groups.

Height is measured using a portable stadiometer (Seca France) and taken to the closest 0.1 cm, and weight is measured without footwear in light clothing to the nearest 100 g with an electronic weighing scale (Seca France). Both instruments are calibrated weekly. BMI is calculated as weight in kilograms divided by height squared in meters. WC is measured using a graduated measuring tape (Seca France), calibrated weekly, with a locking device to the nearest 0.1 cm. WC is taken at the mid-point between the iliac crest and the last rib in expiration. Blood pressure is measured by automatic oscillometry from the non-dominant arm after 5 minutes rest with the mean of two measurements recorded (Riester Ri-Champion Riester, Jungingen, Germany). WHO approved growth charts for male and female children will be used [24].

Fasting plasma glucose and a standard 2-hour 75 g oral glucose tolerance test (OGTT) is performed in adults and glucose solution 1.75 g/kg body weight, to a maximal dose of 75 g is given to those below 16 years following a 12-hour fast as per WHO guidelines [14]. Plasma Glucose, total cholesterol, high density density lipoprotein (HDL), low density lipoprotein (LDL), triglycerides and serum creatinine will be measured by enzymatic colorimetry (Vitros MS 250, Ortho Clinical Diagnostics, Johnson and Johnson, Co, Rochester USA). Fasting plasma insulin will be measured using radioimmunoassay (Immulite, Siemens, Surrey, UK), which has a sensitivity of 4 μU/ml (<24 pmol/l) and intra and interassay coefficients of variation <8%. Insulin resistance will be calculated using the homeostasis model assessment of insulin resistance (HOMA-IR) [25]. Urine albumin to creatinine ratio will be measured by immunoturbidemtry (Vitros 5,1 FS Chemistry System, Ortho-Clinical Diagnostics, Johnson and Johnson Company, Hampshire, United Kingdom) from an early morning urine sample. In subjects below 18 years the Schwartz equation will be used to estimate glomerular filtration rate (GFR) from serum creatinine values [26] and in subjects above 18 years the Modification of Diet in Renal Disease (MDRD) Study equation will be used to estimate GFR [27].

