### Statistical methods and power calculation

Approximately 2300 subjects with ≥2 risk-factors are required in each group (4600 subjects in total) to detect a 25% relative risk reduction at 5 years on the primary composite cardio-metabolic end-point of new onset T2DM, IGT, IFG, hypertension, albuminuria, renal and CVD events with intensive LSM. The study is powered at the 90% level with a type-1 error of 0.05 (2 sided) assuming a 15% incidence of the primary end-point in the control group and including allowance for 25% drop-out of subjects. The proposed 25% relative risk reduction of the composite outcome is derived from the effects of intensive LSM programme reducing the relative risk of new onset T2DM in South Asian IGT patients [1,6].

There will be a pre-specified interim analysis of the composite primary and secondary endpoints at 2 years, as requested by one of the funding bodies (IDF BRIDGES). This analysis will be performed by an independent statistician and the trial investigators will remain blinded to the full data analyses and interim results. All data related to interim analysis will directly forwarded to funding body by the independent statistician and will be strictly confidential and not for public dissemination/publication.

Descriptive statistics will be used for the analysis of demographic and clinical features of the cohort. Two-sided t-tests and chi-square (χ^2^) tests will be used to analyze the comparison between the groups at baseline and during follow-up. Survival curves will be calculated to estimate the cumulative incidence of the composite primary end-point and secondary end-points. The difference between the groups in the primary end-point will be tested by means of the two-sided log-rank test. All analyses of end-points are based on the intention-to-treat principle. Analyses will be performed using STATA software version 10 (Stata Corp, College Station, TX, USA).

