### Definition of primary cardio-metabolic end-points

▪ **New onset T2DM **as indicated by either a fasting plasma glucose of ≥7.0 mmol/l and/or a 2-hr plasma glucose concentration of ≥11.1 mmol/l during an annual follow-up confirmed by repeat 75 g OGTT as per World Health Organization (WHO) criteria [14] or initiation anti-diabetic treatment by the subject's family physician following confirmatory tests.

▪ **New onset IGT **is defined as a plasma fasting glucose <7.0 mmol/l and 2-h glucose 7.8-11.0 mmol/l and IFG as fasting plasma glucose between 6.1 to.9 mmol/l or 5.6 to 6.9 mmol/l [14,15].

▪ **New onset hypertension **is defined as mean brachial blood pressure from 2 readings taken following 5 minutes rest ≥140/90 mmHg or initiation of anti-hypertensive treatment commenced by the subject's family physician as per JNC-7 criteria [13]. In those below 18 years hypertension is defined as blood pressure that is, on repeated measurement, at the 95^th ^percentile or greater adjusted for age, height, and sex [13].

▪ **New onset albuminuria is defined as **urine albumin/creatinine ratio ≥2.5 mg/mmol in males and ≥3.5 mg/mmol in females from early morning sample confirmed on one repeat test.

▪ **New onset renal impairment is **defined as estimated GFR <60 ml/min or doubling of serum creatinine from baseline.

▪ **CVD events **are defined as fatal and not fatal events of Myocardial infarction (MI): Congestive heart failure (CHF): death due to clinical, radiological or post-mortem evidence of CHF, Stroke, vascular revascularisitation and admission for unstable angina.

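### Raw changes in weight, BMI, waist, creatinine and eGFR across ages 5 to 40 are assigned plain t-tests, which loses precision and is hard to interpret, and the eGFR equation changes at 18 during follow-up

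*Protocol article*

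**What the plan says.** Under Secondary objective/endpoints the protocol article lists "changes in: weight, BMI, waist circumference (WC), fasting triglycerides", lipids, serum creatinine and estimated GFR. No age- or sex-standardised score is named for any of these changes. The inclusion criteria admit ages 5 to 40.

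Under Statistical methods and power calculation, two-sided t-tests and chi-square "tests will be used to analyze the comparison between the groups at baseline and during follow-up". The only other comparative methods named are survival curves and a log-rank test for the primary end-point. No covariate or age stratum is mentioned.

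Under Procedures: "In subjects below 18 years the Schwartz equation will be used to estimate glomerular filtration rate (GFR"), and the MDRD equation applies above 18. Follow-up lasts 5 years. No rule covers a participant who passes 18 in that time.

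**The concern.** Over 5 years a child gains weight, waist and creatinine by growing, whereas in an adult the same gain points to adiposity or declining renal function. A t-test on raw change treats the spread between growing and fully grown participants as random error. That makes the test less sensitive to the effect of the intervention on adiposity, which is the mechanism it is meant to work through.

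Interpretation suffers as well. Under Intervention and goals, weight loss is sought in those with raised BMI and waist, while children's growth is checked at each visit so that the intervention does not impair it. A smaller raw gain in a child could be less fat or less growth, and a pooled kg difference cannot separate the two.

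For eGFR, a participant who passes 18 has a change score that subtracts the result of one equation from that of another.

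**Working it through.** **The plan's own figure.** The article states no figure for the continuous end-points, only for the primary composite: "The study is powered at the 90% level", "assuming a 15% incidence of the primary end-point in the control group", a 25% relative reduction (15% to 11.25%) and two-sided alpha 0.05. The two-proportion formula gives 1,702 per arm, and 1,702 / 0.75 = 2,270 after 25% drop-out, against about 2,300 stated. The sample size reproduces and does not depend on this point. It supplies the one documented input used below: 2,300 × 0.75 = 1,725 per arm.

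**Weight change.** Let f be the share of children and d the difference in mean 5-year change between children and adults.

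- Age-adjusted (within-group) variance = f × SD_child² + (1 − f) × SD_adult²
- Variance seen by the plain t-test = within-group variance + f(1 − f)d²
- Difference detectable at 90% power = (1.960 + 1.2816) × SD × √(2/1725) = 3.2416 × SD × 0.03405

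All SDs, growth figures and child shares are assumptions. Set A uses f = 0.2-0.5, d = 10-20 kg and SD 5 kg in both groups. Set B uses f = 0.1-0.5, adults +1 kg (SD 5), and children +10 to +20 kg (SD 6-8), so d = 9-19 kg.

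| Case | Within SD | Pooled SD | Variance ratio | Detectable: adjusted → plain |
|---|---|---|---|---|
| A, f 0.2, d 10 | 5.00 | √(25+16) = 6.40 | 1.64 | 0.55 → 0.71 kg |
| A, f 0.5, d 20 | 5.00 | √(25+100) = 11.18 | 5.00 | 0.55 → 1.23 kg |
| B, f 0.1, d 9, child SD 6 | 5.11 | 5.78 | 1.28 | 0.56 → 0.64 kg |
| B, f 0.1, d 9, child SD 8 | 5.38 | 6.02 | 1.25 | 0.59 → 0.66 kg |
| B, f 0.5, d 19, child SD 6 | 5.52 | 10.99 | 3.96 | 0.61 → 1.21 kg |
| B, f 0.5, d 19, child SD 8 | 6.67 | 11.61 | 3.03 | 0.74 → 1.28 kg |

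Power across set B:

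| True difference | Plain t-test | Child/adult difference removed |
|---|---|---|
| 0.5 kg | 24-72% | 60-82% |
| 1 kg | 72-100% | at least 99% |
| 2 kg | about 100% | about 100% |

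If fewer than 1,725 per arm have a year-5 measurement, both detectable differences rise by the same factor and the ratio is unchanged. BMI, waist and creatinine were not computed separately.

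**Bias check.** In 4,000 simulated null trials (40% children, +15 kg SD 8 against +1 kg SD 5), the mean between-arm difference was −0.005 kg and the t-test rejected in 4.5%. Growth therefore acts through chance imbalance: the SD of the difference in child share is √(2 × 0.4 × 0.6/1725) = 0.0167, and 0.0167 × 14 kg = 0.23 kg of added noise.

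**eGFR step.** Anyone entering at about 13 to 17 passes 18 within 5 years. As an illustration with assumed coefficients (creatinine 0.8 mg/dl, height 170 cm, Schwartz constant 0.413 or 0.70):

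- Schwartz: 0.413 × 170/0.8 = 87.8, or 0.70 × 170/0.8 = 148.7
- MDRD: 175 × 0.8^−1.154 × 18^−0.203 = 125.9
- Step with unchanged creatinine: about +38 or −23 ml/min

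Even the sign depends on the constant, which the article does not give. With an assumed 5-30% of participants crossing 18, a step of 10-40 ml/min and an SD of 12-15, the variance ratio is 1.02 to 3.33. The detectable difference moves from 1.32-1.66 to 1.35-2.61 ml/min.

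**The case against.** The strongest reply is that one general sentence in a condensed article does not say which variables get a t-test, does not say that ages are pooled, and does not rule out covariates. A fuller analysis plan may supply them. It is true that pooling is inferred from the absence of any stated stratification. But the article does name a method for group comparisons during follow-up, and for raw change end-points in this age range that method is a weak choice. The point is about a stated method, not a missing detail.

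The article also treats children separately elsewhere: age-specific BMI and waist cut-offs, growth charts and paediatric blood-pressure percentiles. This shows awareness of the issue, but none of it is carried into the change end-points.

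Using a paediatric equation below 18 and an adult one above is sensible at any single visit. The difficulty lies only in subtracting one from the other. Keeping the paediatric equation in people who have become adults is itself a trade-off.

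A reader might infer that growth and the equation change overwhelm or bias the treatment comparison. The documents do not support that. Allocation is randomised 1:1, both disturbances fall on the arms alike, and a 2 kg difference keeps about 100% power.

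A reader might also infer that the primary result is distorted, because renal impairment, defined as "estimated GFR <60 ml/min or doubling of serum creatinine from baseline", appears among the primary end-point definitions and creatinine is affected by growth. The stated primary objective does not include renal impairment, although the composite in the sample-size paragraph does. The documents give no rate from which an effect could be sized. That reading is not established.

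**Conclusion.** The point holds as one of efficiency and interpretation on secondary end-points. The plain t-test on raw change is valid, with no bias and a nominal type I error, but it discards precision that data already collected would recover. For weight, the variance is about 1.25 to 5 times the age-adjusted variance, and the detectable difference rises from about 0.55-0.75 kg to about 0.65-1.3 kg. The loss matters for differences near 0.5 kg and little at 2 kg. Small differences are plausible, since both arms receive the same advice and goals at different frequency.

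Every numerical input except 1,725 per arm, the two-sided 0.05 level and 90% power is an assumption. The eGFR step follows directly from the Procedures text, but its size, sign and the number of participants affected cannot be determined from the article. The primary log-rank test and the sample size are unaffected.

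**What to change.** 1. Analyse continuous change end-points by ANCOVA, or by a mixed model over annual visits, adjusted for baseline value, age and sex.
2. For those under 18 at entry, use age- and sex-standardised weight, BMI and waist scores.
3. Report children and adults separately alongside the overall result.
4. State in advance one rule that avoids cross-equation eGFR differences. Examples are computing both time points with the same equation, or analysing eGFR change only in participants who do not cross 18. The rule should also cover age exactly 18, since the text says only below and above.

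Baseline value, age and sex are already collected. The cost is analysis-plan wording and slightly more programming, with no change to the sample size, the visits or the primary analysis.

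### Continuous secondary end-points are compared by t-tests alone, which use the baseline value inefficiently and do not by themselves secure the stated intention-to-treat principle under drop-out

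*Protocol article*

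**What the plan says.** Under *Statistical methods and power calculation*, the article assigns two-sided t-tests and chi-square tests to group comparisons: they "will be used to analyze the comparison between the groups at baseline and during follow-up". Survival curves and a log-rank test serve the event end-points. The t-test is therefore the only between-group method named for continuous outcomes, and it is also to be applied to the two arms at baseline.

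The same section states that "All analyses of end-points are based on the intention-to-treat principle" and sizes the trial "including allowance for 25% drop-out of subjects".

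Under *Secondary objective/endpoints*, one list is introduced as changes. It includes "fasting triglycerides, fasting high density lipoprotein (HDL) and low density lipoprotein (LDL) cholesterol", physical activity (IPAQ), depression (PHQ-9) and perceived stress. Quality of life (WHOQOL-Bref) appears in a separate paragraph and is not described as a change.

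The article gives no rule for missing continuous values, and no visit schedule specific to these outcomes.

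**The concern.** Three statements sit uneasily together: a two-sample t-test at follow-up, intention-to-treat for every end-point analysis, and an expected loss of a quarter of the participants. Without a further step, a t-test on a 5-year value, or on the change to it, can only use people who have that value.

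The trial is open and the arms differ in contact (4 one-to-one contacts a year against 1), so the people who leave could differ by arm. If they did, part of an observed difference would reflect who stayed.

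Precision is also at stake. A change score subtracts the whole baseline value whatever its correlation with follow-up, and a raw follow-up value leaves baseline out. Neither is the most precise use of data in hand.

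Finally, testing the arms against each other at baseline asks whether chance produced a difference that, under proper randomisation, can only be due to chance.

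**Working it through.** **1. The plan's own figure.** The inputs are in *Statistical methods and power calculation*: "assuming a 15% incidence of the primary end-point in the control group", sized "to detect a 25% relative risk reduction at 5 years" (15% to 11.25%), 90% power and two-sided 0.05. The two-proportion formula gives 1,702 per group, and 1,702 / 0.75 = 2,270 after drop-out. With continuity correction the figures are 1,755 and 2,340. The stated 2,300 or so is reproduced, so nothing below concerns the primary sample size.

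**2. Participants with a 5-year value.** 2,300 × 0.75 = 1,725 per arm at the planned drop-out. The 25% is an allowance made for the primary end-point; applying it to the secondary outcomes is an assumption.

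**3. Precision.** Standardise the outcome to SD 1 at both times, with baseline-to-follow-up correlation r. The documents give no r; the main range assumed is 0.4 to 0.7. The relative variance of the arm difference is:
- t-test on the follow-up value: 1
- t-test on change: 2(1 − r)
- baseline-adjusted analysis (ANCOVA): 1 − r²

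Adjusted against change: (1 − r²) / [2(1 − r)] = (1 + r)/2. Adjusted against raw follow-up: 1 − r².

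| r (assumed) | Adjusted / change | Adjusted / raw follow-up |
|---|---|---|
| 0.4 | 0.70 | 0.84 |
| 0.5 | 0.75 | 0.75 |
| 0.6 | 0.80 | 0.64 |
| 0.7 | 0.85 | 0.51 |

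For outcomes defined as changes, this means 30% (r = 0.4) down to 15% (r = 0.7) fewer participants for equal precision. For quality of life, if tested on its follow-up value, it means 16% up to 49% fewer.

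As power for a true difference of 0.10 SD with 1,725 per arm:
- r = 0.5: 84% for either t-test, 92% adjusted
- r = 0.7: 84% on raw follow-up, 97% on change, 98% adjusted

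**4. Bias from selective drop-out.** This is a simulation with assumed inputs: 2,300 per arm, no true effect, random-intercept variance 0.5, autoregressive residual variance 0.5 (correlation 0.5), annual drop-out about 5.75%, and 26–30% lost in all. Log-odds of drop-out rise with the last value in the intensive arm only. Entries are bias in SD units, with the false-positive rate in brackets.

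| Analysis | 0.5 per SD | 0.8 per SD |
|---|---|---|
| t-test on raw 5-year value | −0.09 (75%) | −0.15 (about 100%) |
| t-test on change | 0.014 (6.5%) | 0.026 (11.5%) |
| ANCOVA, completers only | −0.037 (23%) | −0.06 (55%) |
| Sequential regression on all annual values | 0.001 | 0.001 |

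Repeat runs put the change-score false-positive rate at about 5–8% and 11%. If only year-2 and year-5 values are available, −0.021 to −0.036 SD of bias remains over the two slopes. If drop-out depends on the value equally in both arms, all biases are about zero.

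**5. Baseline tests.** With, say, 30 baseline variables (assumed), 30 × 0.05 = 1.5 significant differences are expected by chance alone.

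**The case against.** The strongest reply is that a change-score t-test is valid under randomisation, that only secondary outcomes are involved, and that at r = 0.7 the power gain for 0.10 SD is from 97% to 98%. This stands as a limit on size: the gain matters more at lower r, and r is unknown.

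Three stronger readings are tempting, and the documents do not support them.

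- *The t-tests ignore baseline.* Lipids, activity, depression and stress are defined as changes, so baseline enters. Only quality of life is not stated that way.
- *The intention-to-treat claim fails.* Completers-only use is an inference. The article states no missing-data rule, a t-test can be combined with imputation, and such rules are commonly left to a fuller document. What can be said is that the named test does not by itself secure the principle.
- *False-positive rates of 75% to 100%.* These belong to raw follow-up values under assumed one-arm selective drop-out. For change scores the same scenario gives a small bias.

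Two further objections stand and shape the remedy. First, baseline adjustment alone does not remove the bias: in the assumed scenario, completers-only ANCOVA is more biased than the change score. The protection comes from repeated follow-up values. The article mentions annual follow-up in the diabetes definition and an interim analysis of secondary end-points at 2 years, but does not state annual measurement of these outcomes. Second, a mixed model with baseline as covariate also leaves out participants with no follow-up value, about 6–7% in the simulated setting.

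**Conclusion.** The point holds as one of efficiency and of an unsecured principle. The t-test is the only method named for these end-points, and a baseline-adjusted longitudinal model is better at almost no cost. The sure gain is precision: equivalent to 15–30% fewer participants for outcomes defined as changes, assuming r of 0.7 to 0.4 and equal variance at both times.

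The bias argument is conditional. It needs drop-out that depends on the outcome differently by arm, for which the documents give no figure. Even then it is about 0.01 to 0.03 SD for change scores, and larger for raw follow-up values, which may apply to quality of life. How far a longitudinal model reduces it depends on how often these outcomes are measured.

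The between-arm tests at baseline are uninformative whatever one assumes about r or drop-out.

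**What to change.** - For the continuous secondary end-points not related to growth (lipids, physical activity, depression, stress, quality of life), replace the t-tests with one linear mixed model per outcome. Use all collected follow-up values as responses, the baseline value as covariate, and arm, visit and arm-by-visit terms. Report the 5-year arm difference with its 95% CI.
- State that the model assumes drop-out is explained by observed values, and name the visits that contribute.
- Specify a sensitivity analysis for randomised participants who have no follow-up value, since the model does not include them.
- Delete the between-arm significance tests at baseline and present baseline data descriptively.

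The cost is a change of analysis wording plus the sensitivity analysis. No new data are needed if the model uses only what is collected. The drop-out assumption cannot be verified from the data, but it is weaker than the one a completers-only t-test makes.

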### Exclusion Criteria

#### During screening

• Subjects with no or one identifiable risk factor

• Subjects with diagnosed end-points (T2DM, CVD, hypertension and renal disease)

• Subjects on any form of medication used for the treatment of diabetes, hypertension, renal disease or dyslipidaemia

• Any active communicable or NCD such as cancer, asthma or other forms of chronic lung disease, depression, tuberculosis.

• Pregnant women

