#### During the primary prevention intervention trial

• Subjects who reach one or more of the following cardio-metabolic end-points; T2DM, CVD, hypertension, and albuminuria.

• Subjects initiated on any form of medication used for the treatment of diabetes, hypertension, renal disease or dyslipidaemia by their family physician or other medical physician.

• Pregnancy at any stage of the study

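### Survival curves are named for regression of IGT/IFG although progression to T2DM removes the participant; if progressors are censored, the regression percentage in each arm is overstated (a minor point on a secondary estimate)

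*Protocol article*

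**What the plan says.** Four places in the protocol article bear on this.

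- **Secondary objective/endpoints** includes "regression of IGT and IFG" in its list.
- **Statistical methods and power calculation** states: "Survival curves will be calculated to estimate the cumulative incidence of the composite primary end-point and secondary end-points". Regression is not excepted, and no competing-event method is named. The same section lists "Two-sided t-tests and chi-square" tests for group comparisons at baseline and during follow-up, assigns the log-rank test to the primary end-point, and adds: "All analyses of end-points are based on the intention-to-treat principle".
- **Exclusion Criteria, During the primary prevention intervention trial** lists "Subjects who reach one or more of the following cardio-metabolic end-points; T2DM, CVD, hypertension, and albuminuria". It also lists "Subjects initiated on any form of medication used for the treatment of diabetes, hypertension, renal disease or dyslipidaemia by their family physician" and "Pregnancy at any stage of the study".
- **Exclusion Criteria, During screening** does not name IGT or IFG, and the Procedures section has a glucose tolerance test before randomisation. Participants with IGT or IFG at baseline can therefore enter, and there is a population in whom regression can be assessed.

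**The concern.** A participant with IGT or IFG can leave that state in two opposite ways: return to normal glucose, or progress to T2DM. The in-trial criteria take the second group out, so no later regression can be recorded for them. In an ordinary survival curve for time to regression they would be censored at that point. Censoring in effect credits them with the same future chance of regressing as those still under observation. One minus the curve then estimates regression in a hypothetical setting without progression, not the proportion who actually regress.

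The regression percentage is what a reader would take as the share of pre-diabetic young people returned to normal glucose, and the error always flatters it. Regression, progression and persistence, reported side by side, would add to more than 100%. A comparison of the two curves would also miss any gain in regression that arises because fewer participants in the intensive arm progress.

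**Working it through.** **The plan's own figures.** The article gives no figure for regression, or for progression among participants with IGT/IFG, so there is none to reproduce on this point. Its sample size concerns the primary composite. That does reproduce: 15% against 11.25%, 90% power and two-sided 0.05 give 1702 per group, and 1702/0.75 = 2270, against about 2300 stated.

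**Inputs from the article.** 4600 participants, 1:1 allocation, 5 years, annual follow-up for the glucose end-points. The Background gives a pre-diabetes prevalence of 10–15% in South Asian adults.

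**Assumptions.**
- Baseline prevalence of IGT/IFG 5%, 10% or 15% (the lower value because children are included). Per arm: 4600 × 0.05/2 = 115, 4600 × 0.10/2 = 230, 4600 × 0.15/2 = 345.
- Each year a participant still in IGT/IFG regresses with probability r or progresses with probability p. No other loss.

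**Formulas over five annual visits.**
- Proportion who regress (cumulative incidence): CIF = r/(r+p) × [1 − (1−r−p)^5]
- One minus the survival curve with progressors censored: 1−KM = 1 − (1−r)^5
- Proportion who progress: p/(r+p) × [1 − (1−r−p)^5]
- Standard error in one arm: √[CIF(1−CIF)/n]

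**Base case, r = 0.10, p = 0.04.**
- CIF = 0.10/0.14 × (1 − 0.86^5) = 0.714 × 0.5296 = 37.8%
- 1−KM = 1 − 0.90^5 = 41.0%
- Excess 3.1 points, which is 0.7, 1.0 and 1.2 standard errors at 115, 230 and 345 per arm.
- Progression 15.1%, persistence 0.86^5 = 47.0%. Regression by 1−KM plus these two gives 41.0 + 15.1 + 47.0 = 103.1%.

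**Other rates.**

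| r per year | p per year | CIF | 1−KM | Excess (points) |
|---|---|---|---|---|
| 0.06 | 0.01 | 26.1% | 26.6% | 0.5 |
| 0.06 | 0.02 | 25.6% | 26.6% | 1.0 |
| 0.10 | 0.01 | 40.1% | 41.0% | 0.8 |
| 0.10 | 0.06 | 36.4% | 41.0% | 4.6 |
| 0.10 | 0.10 | 33.6% | 41.0% | 7.3 |
| 0.15 | 0.01 | 54.5% | 55.6% | 1.1 |
| 0.15 | 0.10 | 45.8% | 55.6% | 9.9 |

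Over r = 0.06–0.15 and p = 0.02–0.10 the excess is 1.0 to 9.9 points. A continuous-time version with r = 0.05–0.15 and the same p gives 1.0 to 10.0. On a much wider grid (r = 0.02–0.30, p = 0.01–0.18) it gives 0.2 to 20.9.

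**Between-arm contrast.** Take r = 0.10 in both arms and progression 25% lower in the intensive arm. The 1−KM difference is then 0. The CIF differences are:
- p = 0.04 against 0.03: 38.6% − 37.8% = 0.8 points
- p = 0.06 against 0.045: 37.5% − 36.4% = 1.1 points
- p = 0.10 against 0.075: 35.3% − 33.6% = 1.7 points

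At 230 per arm the standard error of the difference is about 4.4–4.5 points, so these are 0.2 to 0.4 standard errors.

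**The case against.** The strongest objection is that censoring is an inference. The article speaks of survival curves but names neither Kaplan-Meier nor a censoring rule, and it is a condensed account whose full protocol and analysis plan are not shown. That stands, and it is why the size is stated conditionally. It does not dispose of the point. The article does not leave the estimator open: it assigns survival curves to the cumulative incidence of the secondary end-points. Combined with removal at T2DM, censoring is the ordinary consequence.

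The sentence also cannot be literal for every secondary end-point, since changes in weight, lipids or questionnaire scores have no cumulative incidence. It may be shorthand for the incident end-points only. That is a fair reading, but nothing in the text takes regression out.

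The chi-square tests could be applied to the proportion regressed, with progressors kept in the denominator. The text permits this, but offers those tests for comparing groups and gives the estimation of cumulative incidence to the curves. The intention-to-treat statement does not say how a competing event enters a curve.

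A reader might infer three stronger things, none of which the documents support:

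- **That the article states progressors are censored, or that the excess is a known 1 to 10 points.** It gives no rates. The number needed to treat of 6.4 quoted in the Background carries no time horizon there, and the prevention studies described were mostly in older subjects, so it cannot fix a progression rate at ages 5–40.
- **That the treatment comparison is materially distorted.** It moves by a fraction of a standard error, and new-onset T2DM, as a component of the composite, is itself a secondary end-point, so a benefit through fewer progressors is still reported.
- **That the other removals create the same problem.** Hypertension, albuminuria and pregnancy are not the opposite outcome to regression. They raise a censoring question, not this one.

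**Conclusion.** The point holds as a minor one about a secondary estimate. The article names an estimator that suits regression of IGT/IFG badly, because the exit that removes a participant is the opposite outcome. If progressors are censored, the direction is certain whenever anyone progresses: the regression percentage is too high in each arm.

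The size rests wholly on assumed rates, annual assessment and no other loss, although the plan itself allows for 25% drop-out. On those assumptions it is about 1 to 10 points for regression of 6–15% and progression of 2–10% a year, 3.1 points at 10% and 4%, and about 1 point or less at 1% a year progression. The between-arm contrast changes by about 0.8–1.7 points in the scenarios worked. The primary composite and its log-rank test are untouched by this point, since T2DM is one of the composite's components.

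**What to change.** In Statistical methods and power calculation, take regression of IGT/IFG out of the survival-curve sentence and add its own:

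- **Population:** participants with IGT or IFG at the glucose tolerance test before randomisation, by assigned arm.
- **Estimator:** cumulative incidence function (Aalen-Johansen) for first regression, with T2DM as a competing event. T2DM would include the start of anti-diabetic treatment, in line with the article's own definition of new-onset T2DM.
- **Comparison:** Gray's test.
- **Reporting:** the progression proportion beside the regression proportion in each arm.

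An alternative is the proportion with normal glucose at 5 years, counting every progressor as not regressed. This is a different estimand and not an equivalent: it describes status at 5 years, and someone who regresses and later relapses counts in the first quantity but not in the second. The plan should choose one and say which.

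The cost is one or two sentences and a standard routine, with no new data, visits or participants. The downside is a somewhat less favourable regression percentage in both arms.
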